## Abstract

Background and aim: Recent preclinical studies have confirmed that inhibiting the MAP kinase pathway can induce the re-differentiation of radioiodine (RAI)-refractory (RAIR) follicular cell thyroid cancers (TCs). The aim of this trial is to investigate whether the combination of kinase inhibitors (KIs) with myo-inositol (MI) can induce or potentiate the re-uptake of RAI in cancer cells. Overview and methods: This is an open label, non-pharmacological, multicenter, randomized pilot study. Patients will be divided into two groups: (1) a control group in which patients are treated with KIs (subgroup a: trametinib plus dabrafenib; subgroup b: lenvatinib); (2) a group in which patients (divided into the two subgroups) are treated with the same KIs in addition to MI. After 30 days of MI treatment, all patients, treated with levothyroxine (L-T4) at a semi-suppressive dosage as per clinical practice, will be stimulated with recombinant human TSH (rhTSH) (days 31 and 32). On day 35, the patients will be subjected to whole-body scintigraphy, with hybrid imaging where possible (SPECT/CT), after the administration of diagnostic activity (185–222 MBq of 123-I in accordance with the SNMMI/EANM guidelines. Blood samples will be collected before starting MI therapy (day 0); after 30 days of MI therapy; and then on days 31, 32, 33, 34, and 35 after MI therapy. Quality of life (QoL) will be assessed at the beginning of the MI treatment and at the end of its administration. The primary endpoint is the restoration of 123-I uptake in RAIR-TC patients already on KI therapy alone and on KI therapy plus MI. The restoration of 123-I uptake in target lesions will be evaluated. Conclusions: MI may have a synergistic effect at the cellular level, and the possible increase in the re-differentiation of RAIR-TC in patients treated with KIs plus MI may have great clinical relevance. The re-uptake of RAI will be evaluated as the primary endpoint, and Tg values and QoL will be evaluated as the secondary endpoints. The main limitation of this study is that we do not investigate any clinical effects. We will have to postpone the clinical analysis to a later date after the administration of RAI for therapeutic purposes.

## 1. Introduction

Thyroid cancer (TC) is the most common endocrine malignancy, and follicular cell TC is the most frequent form [1]. Human samples and animal models have led to the identification of early driver mutations (mainly BRAF V600E and RAS family), late event changes, and more recently new potential players that favor cancer transformation and/or progression [2]. At the molecular level, the Mitogen-Activated Protein Kinase (MAPK) and Phosphatidylinositol 3-kinase/Protein Kinase B (PI3K/Akt) pathways are usually dysregulated, accompanied by impaired expression of the Sodium/Iodine Symporter (NIS). Follicular cell-derived TC, with the exception of poorly differentiated TC and anaplastic TC, conserves some NIS expression in the basal plasma cell membrane. The NIS amasses iodine in the thyroid cell by transporting two sodium ions and one iodine ion into the cytosol, and iodine is then incorporated and stored in thyroglobulin, which is referred to as organification. Radioiodine (RAI) thus represents one of the first theragnostic agents in medicine. RAI is the cornerstone of treatment, after total thyroidectomy (TT), for adjuvant purposes in intermediate- and high-risk differentiated follicular cell-derived TC. RAI is also the main therapeutic option in the metastatic disease, which occurs in fewer than 10% of cases but represents the most frequent cause of TC-related death. However, unfortunately, a percentage of these metastatic cancers can become RAI-refractory (RAIR), and although rare, metastasis can be RAIR even from the initial diagnosis [3,4,5,6]. Although there is no universal definition of RAIR, RAIR-TCs have been classified into four categories, as shown in Supplementary Table S1.

The possible choice of therapeutic strategies for RAIR-TC is completely different. Local therapy, primarily surgery, is implemented where possible, but in the case of significant and diffuse progression of widespread metastatic disease, only systemic therapy offers a reasonable chance of success. An effective systemic therapy for RAIR-TC was a long-unmet need, but in the last few years, protein kinase inhibitors (KIs) have represented a turning point for the treatment of these tumors [7,8] by improving both progression-free and overall survival. In addition, as discussed below, treatment with KIs has been shown to restore some differentiation in RAIR-TC.

Protein kinases catalyze the transfer of the phosphate group from a nucleoside triphosphate donor to target proteins, resulting in a conformational change in the protein, which alters its function. Protein kinases are frequently involved in signal transduction (membrane signals, i.e., receptors) or in post-receptor cascade activation with the regulation of growth, cell cycle, apoptosis, and differentiation. Notably, among all these complex intracellular signal transduction pathways mediated by protein kinases, the MAPK and PI3K/Akt pathways are well known to be implicated in thyroid tumorigenesis. KIs are small molecules that, through different mechanisms, can interfere with the active phosphorylating domain of protein kinases, thus blocking their enzymatic function and the entire post-receptor cascade.

Several studies have demonstrated that MAPK pathway activation is associated with dedifferentiation and, in particular, NIS repression. The Cancer Genome Atlas (TCGA) Research Network highlighted that BRAFV600E-mutated papillary TC (PTC) (which has the strongest activation of the MAPK pathway) shows the most dedifferentiated state, i.e., a low expression of some thyroid differentiation genes such as the gene encoding the NIS (SCLC5A5), thyroglobulin (Tg), or thyroid peroxidase (TPO). The anti-proliferative effects of KIs may thus re-induce the ability to take up iodine, and the possible role of re-differentiation is currently under investigation in several trials.

Several in vitro studies have demonstrated an increase in NIS expression and/or iodine uptake in human TC-derived cell lines with different MAPK pathway KIs. These were, specifically, selective KI inhibitors (sKIs), namely BRAFV600E sKIs, such as vemurafenib [9,10] and dabrafenib [11]; MEK inhibitors, such as selumetinib [11,12]; and multi KIs (mKIs), such as cabozantinib [13] and sorafenib [12,13].

The first clinical phase II study to test the mKI sorafenib reported that, of the 20 patients evaluated for re-differentiation, only one showed a weak restored uptake of RAI in an occipital skeletal metastasis on a diagnostic whole-body scan (WBS); however, this was not confirmed on the therapeutic WBS [14]. Renewed interest in the re-differentiation strategy arose after a study by the James Fagin laboratory (Memorial Sloan-Kettering Cancer Center) [15]. In this latter study, an ingenious mouse model expressed the BRAFV600E oncogene in thyrocytes, and the expression of the BRAFV600E could be switched on or off with the administration or withdrawal of doxycycline. A MEK inhibitor (selumetinib) or BRAFV600E inhibitor (dabrafenib) partially restored thyroid-specific gene expression and RAI uptake. Following this preclinical in vivo study, a pioneer study by the Memorial Sloan-Kettering Cancer Center by Ho et al. in 24 patients with PTC or follicular-TC (FTC) or PDTC confirmed the ability of selumetinib to restore RAI uptake in 44% of the BRAFV600E-mutated DTC patients, who were then treated with 131I, resulting in partial tumor responses in 11% of these patients [16].

More recently, a considerable number of preclinical studies have confirmed that inhibiting the MAP kinase pathway can induce re-differentiation and tumor responses in BRAFV600E-mutated TC with clinical benefits [17,18,19,20,21]. Overall, these studies show that cellular de-differentiation may be reversible in terms of both the re-uptake of iodine and the synthesis of specific proteins such as thyroglobulin. However, during treatment, on-target and off-target mutations may be a potential general mechanism of resistance. Most in vitro and in vivo studies have used sKIs; however, some studies have also shown that cabozantinib and lenvatinib increased RAI uptake [13,22,23]. This is not surprising considering that, although mKIs have multiple targets, and although the main effect of lenvatinib is on vascular endothelial growth factor receptor (VEGFR) 1–3, this drug also interacts with platelet-derived growth factor receptor (PDGFR) and the PI3K/Akt pathway.

The literature data also suggest that myo-inositol (MI) may play a role in potentiating the action of KIs at various levels.

MI is a carbocyclic polyol and belongs to the inositol (IS) family, which consists of nine possible structural isomers. MI is the IS most widely distributed in nature and is present in fresh fruits, vegetables, cereals, legumes, and nuts. However, MI is also endogenously synthesized from glucose-6-phosphate and, in some tissues, represents approximately 99% of intracellular IS. MI is a fundamental component of structural lipids in cell membranes such as phosphatidylinositol (PI) and different phosphatidylinositol phosphates (PIPs), which are precursors for many other IS-containing compounds involved in signal transduction, vesicle trafficking, cell differentiation, and growth.

The generation of MI and its intracellular derivates is partly under the control of TSH. In fact, at slightly higher physiological concentrations, TSH activates the phospholipase C-dependent inositol phosphate Ca^2+^/diacylglycerol (DAG) pathway, with the formation of mainly inositol 1,4,5-triphosphate (IP3). IP3 increases the concentration of intracellular Ca^2+^ by favoring its release from the endoplasmic reticulum. Calcium is essential for DUOX2 activation and H_2_O_2_ generation and activates the entire DUOX2/TPO complex, iodine organification, and thyroid hormone synthesis [24,25]. In addition, other IS polyphosphates (3.4 and 3.4.5 polyphosphates) can inactivate Akt, which is a serine/threonine-specific protein kinase also known as protein kinase B. Because activating mutations in proteins of the PI3K/Akt/mTOR pathways is implicated in tumorigenesis and the dedifferentiation of thyroid cells, the abovementioned IS polyphosphates may play a protective (anti-tumoral) role and specifically increase tumor re-differentiation [26]. The last intriguing potential effect of the IS family in potentiating iodine uptake in thyroid cells is the positive role of PIP5K in the recruitment and activation of EZRIN, which binds to NIS and increases its membrane residency [27].

In summary, MI may increase the uptake and retention of iodine inside the tumor cell and block the dedifferentiation pathway, thus acting in a synergistic fashion with KIs. The aim of this trial is thus to investigate whether the combination of MI with sKIs and mKIs can induce or potentiate the re-uptake of RAI in cancer cells. Moreover, our protocol regarding the use of KIs as re-differentiating agents differs significantly from most other protocols.

## 2. Materials and Methods

### 2.1. Overview of Trial Design

This is an open-label, non-pharmacological, multicenter, randomized pilot study. Data will be collected on RAIR-TC patients being treated with KIs as per clinical practice in multiple institutions across Italy. The protocol was approved by the Ethics Committee (UniCamillus, Rome E00114-2025). The enrollment of patients will start after the protocol’s approval by the ethics committee of each center and will continue until the target sample size has been achieved (see below). The site personnel will capture all the data (epidemiological, clinical, pathological, and biochemical) electronically at the study site in an Excel database provided by the coordinating center.

The MI supplement will be shipped to the hospital pharmacy of the coordinating center and satellite centers. The product will be delivered by the pharmacy to the investigator at each center, who will then dispense it to the patients enrolled in the MI treatment group. The product can be stored at room temperature.

### 2.2. Eligibility Criteria and Study Design

Patients meeting the eligibility criteria described in Supplementary Table S2 will be included. In summary, RAIR-TC patients will need to have had next-generation sequencing (NGS) analysis for possible mutations. Eligible patients will have a BRAF mutation (treated with sKIs), no mutations, or non-targetable mutations (treated with mKIs). Patients must have been taking KIs for at least four months.

All patients will need to give their written informed consent to be included in the study.

The trial’s design is summarized in Figure 1. Patients will be divided into 2 groups: (1) a control group in which patients are treated with KIs (subgroup a: trametinib plus dabrafenib; subgroup b: lenvatinib); (2) a group (divided into the same subgroups), in which patients are treated with the same KIs in addition to MI. Comparisons will be made between the same subgroups.

MI has a half-life of less than 24 h, and a complete steady state can be achieved in about 4–5 days. However, a longer administration (30 days) helps to ensure an effect on the various metabolic activities. After 30 days of MI treatment, all patients, treated with L-T4 at a semi-suppressive dosage as per clinical practice, will be stimulated with recombinant human TSH (rhTSH) (days 31 and 32). On day 35, patients will be subjected to WBS, with hybrid imaging where possible (SPECT/TC), after the administration of diagnostic activity (185–222 MBq) of 123-I in accordance with the SNMMI/EANM guidelines [28]. Blood samples will be collected before starting MI therapy (day 0); after 30 days of MI therapy; and then on days 31, 32, 33, 34, and 35 after MI therapy. The laboratory assessments are reported in Supplementary Table S3. Quality of life (QoL) will be assessed at the beginning of the MI treatment and at the end of its administration.

Patients will be withdrawn from the study if they experience any side effects from the MI or if they experience adverse unmanageable effects from the KIs, although no known side effects of MI have been reported to date.

The study will be terminated early if there is premature evidence of superiority in the MI group. The study will conclude upon evaluation of the primary endpoint.

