### 2.3. Sample Size and Procedure

We estimate that the difference between the two percentages of subjects in terms of iodine uptake at the end of treatment will equal 30% (for example, 60% in the experimental group and 30% in the control group). We also set the alpha error and power at 5% and 80%, respectively. Given these conditions, 42 patients per group will be necessary for the effect size indicated above to lead to a statistically significant result. A total of 84 patients will therefore need to be enrolled. A chi-square test will be used for the primary endpoint. Univariate and multivariate tests will be used for secondary endpoints. A multivariate logistic regression will be performed adjusting for gender and age.

The patients will be enrolled with a 1:1 ratio in either the control (KI group) or treatment MI (KI plus MI group) groups. The randomization list will be generated using Excel. We will include RAIR-TC patients being treated with KIs as per clinical practice. The enrolled patients will be divided into groups based on the KI type and then into two subgroups: KIs only vs. KIs plus MI. All patients will need to give their written informed consent to be included in the study. If not already available for all patients, an NGS molecular panel will be performed to look for somatic mutations. Each patient will be identified by a two-digit code and patient initials, which are the only identification elements and will only be used for the purposes of the study. Clinical data will be collected during the randomization, on the first (Day 1) and last day (Day 30) of the supplementation with MI (in both the KI and KI plus MI groups), and then on the day of the whole-body scintigraphy (Day 35).

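### Section 2.2 compares MI within each KI subgroup, but section 2.3 sizes the 84 patients for one pooled comparison; the stated 80% power holds only for the pooled one

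*Protocol article*

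**What the plan says.** Section 2.2 defines two KI subgroups in each arm, trametinib plus dabrafenib (a) and lenvatinib (b), and then states: "Comparisons will be made between the same subgroups". Section 2.3 repeats the structure: "The enrolled patients will be divided into groups based on the KI type and then into two subgroups: KIs only vs. KIs plus MI".

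The sample size in section 2.3 takes no account of KI type. It assumes a 30-point difference, for example "60% in the experimental group and 30% in the control group", and adds: "We also set the alpha error and power at 5% and 80%, respectively". It concludes that "42 patients per group will be necessary for the effect size indicated above to lead to a statistically significant result", and that "A total of 84 patients will therefore need to be enrolled". Allocation is also described for two groups only: "The patients will be enrolled with a 1:1 ratio in either the control (KI group) or treatment MI (KI plus MI group) groups". One chi-square test, in the singular, is named for the primary endpoint.

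The article does not say whether that test pools the KI types or is run within each. It gives no target number per KI type and does not call the within-KI comparisons secondary or exploratory.

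**The concern.** Both the comparison rule and the sample size are stated, and they describe different analyses. So this is not a detail that an article may leave to an analysis plan. On the literal reading of section 2.2 there are two comparisons, each using only part of the 84 patients, and neither has the 80% power that section 2.3 states. On the pooled reading of section 2.3, the sentence in section 2.2 misdescribes the main comparison.

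The risk lies in interpretation. The two KI regimens go to different molecular populations, and the Discussion presents the lenvatinib part as a novelty, so readers will look at the result for each KI. If MI adds the same 30 points with both regimens, two comparisons at about 50% power will often disagree, and the disagreement can be mistaken for a drug-specific effect.

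**Working it through.** **Inputs.** From section 2.3: p1 = 0.60, p2 = 0.30, alpha 5%, power 80%, 42 per group, 84 in total, 1:1 allocation. Assumptions, because the article does not state them: two-sided testing (this reproduces the stated n), the same 60% and 30% in both KI types, and the split of patients between KI types (a range is shown).

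**1. Reproduce the stated figure.** Pooled-variance formula without continuity correction, with mean rate p = 0.45:

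n = [z(0.975)·√(2p(1−p)) + z(0.80)·√(p1(1−p1) + p2(1−p2))]² / (p1 − p2)²

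= [1.960 × √0.495 + 0.842 × √0.45]² / 0.09 = [1.379 + 0.565]² / 0.09 ≈ 41.97, so 42 per group.

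This matches the article. Power at 42 per arm is 80.0%.

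**2. Power within a KI type.** With m patients per arm in that KI type:

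power = Φ{ [0.30·√m − z(1−α/2) × √0.495] / √0.45 }

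For m = 21 (equal split) and α = 5%: 0.30 × 4.583 = 1.375; (1.375 − 1.379)/0.671 = −0.006; Φ = 49.8%. Exact enumeration of the uncorrected chi-square test gives 49.5%.

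| Split of the 42 per arm | Power, two-sided 5% per test |
|---|---|
| 21 / 21 | 49.8% / 49.8% |
| 14 / 28 | 35.1% / 62.2% |
| 10 / 32 | 26.1% / 68.2% |

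In none of these splits does either KI type reach 80%. If the 5% is divided (2.5% per test), z rises to 2.241 and power at 21 per arm falls to 38.2%.

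**3. Chance of discordant results.** Equal split, same true effect in both KI types: both significant 0.498² ≈ 25%; exactly one 2 × 0.498 × 0.502 ≈ 50%; neither about 25%.

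**4. False positives.** Two independent tests at 5% each: 1 − 0.95² = 9.75%. Exact enumeration at 21 per arm with a 30% rate in every cell gives each uncorrected chi-square test a size of about 5.6%, hence 1 − 0.944² ≈ 10.9%.

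**5. Size needed for 80% power within each KI type.** At 5% per test: 42 per arm per KI type, 4 × 42 = 168 in total. At 2.5% per test: 51 per arm per KI type, 4 × 51 = 204 in total.

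**The case against.** The strongest reply is that section 2.3 already describes a pooled primary analysis: one effect size, one n per group, one chi-square test, one 1:1 allocation. The section 2.2 sentence names no endpoint, test, alpha or primary status. It may mean only that like is compared with like, so that dabrafenib plus trametinib patients are not set against lenvatinib patients, which fits a comparison stratified by KI type. The trial is also called a pilot.

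Much of this stands. A reader might infer that the plan is committed to two primary within-KI tests and is therefore underpowered as designed. The documents do not support that: the statistical statements in section 2.3 point to pooling, and the pooled calculation is correct. A reader might also infer that each comparison has a firm 50% power while the two share one 5% alpha. No sharing is stated, and the figures belong to different cases: 50% goes with a full 5% per test, 38% with a shared 5%. Nor is 50% firm, because the article fixes no split between KI types and offers 60% and 30% only as an example. Finally, the lack of a multiplicity rule is no defect in itself, since an analysis plan may hold it; the error rate matters only if two tests are intended.

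What does not fall away is the conflict. The only stated comparison rule is within subgroup and the only stated sample size is pooled. The pilot label does not remove this, because section 2.3 sets alpha, power and a significance target.

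**Conclusion.** The concern holds as an unreconciled contradiction between sections 2.2 and 2.3 over which comparison the trial is built on. The 80% power is right for all KI plus MI against all KI patients, and for that comparison only. If the comparisons in section 2.2 are meant, power per KI type is about 50% with an equal split and ranges from about 26% to 68% over splits down to 10 and 32 per arm. It is about 38% with an equal split at 2.5% per test. Familywise error with two uncorrected 5% tests is about 10 to 11%. These figures assume 60% versus 30% in both KI types and two-sided tests. Under a uniform true effect and an equal split, about half of such trials would show exactly one significant KI type, so the point should be settled before any data are seen.

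**What to change.** In section 2.2, replace the comparison sentence with wording such as: *The single primary comparison is KI plus MI versus KI alone in all randomised patients, stratified by KI type (for example, a Mantel-Haenszel test). Within-KI results are descriptive: the difference in responder proportions with its 95% confidence interval, and an estimate of the MI-by-KI interaction.* In section 2.3, name the same test and state that the 80% power applies to this comparison only.

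This costs a few sentences, leaves the sample size at 84, and uses the KI grouping by which patients are already divided. The real cost is that no separate efficacy claim per KI type can be made.

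If the investigators do intend within-KI tests as primary, the stated 80% must be replaced by the subgroup power above, with the assumed split and the alpha per test stated. Keeping 80% in each KI type would instead take 168 patients (5% per test) or 204 (2.5% per test), with target numbers per KI type.

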### 2.4. Study Aims

The objective of the study is to evaluate the efficacy of 2 g of MI twice a day for RAIR-TC in inducing the re-uptake of RAI in patients during KI therapy. Although evaluating the effectiveness of the chronic treatment of KIs on re-differentiation is not one of the endpoints of the study, some possible speculations are discussed below.

The primary endpoint is the restoration of 123-I uptake in RAIR-TC patients already on KI therapy alone and on KI therapy plus MI. The restoration of 123-I uptake will be evaluated in target lesions. In the case of multiple lesions, only re-uptake in a target lesion will be considered. A regional target/background ratio of more than 4 and a 2-fold higher iodine uptake than the mean uptake in liver parenchyma according to visual assessment will be considered to indicate responders.

The secondary endpoints are (1) the thyroglobulin trend as a secondary marker of differentiation and (2) the safety and QoL of these patients.

Safety will be assessed according to the clinical symptoms and laboratory parameters. This includes the monitoring of adverse events as defined in the Common Terminology Criteria for Adverse Events (CTCAE) v5.0. All the investigators involved in the study will be responsible for reporting all adverse events occurring during the study.

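### Any MI side effect takes the patient out of the study, a rule only the MI arm can trigger, and enrolment of 84 leaves no reserve for lost Day 35 scans

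*Protocol article*

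**What the plan says.** Section 2.2 sets two grounds for withdrawal. The first is "Patients will be withdrawn from the study if they experience any side effects from the MI", with no threshold of severity. The second, in the same sentence, is KI toxicity that cannot be managed. The sentence ends by noting that no MI side effects have been reported so far. The same section gives one scan, on Day 35, after 30 days of MI, and measures QoL at the start and end of MI.

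Section 2.1 describes an open-label trial in which MI is dispensed only to the MI group.

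Section 2.3 assumes a 30-point difference ("for example, 60% in the experimental group and 30% in the control group") and continues: "We also set the alpha error and power at 5% and 80%, respectively". It concludes that "42 patients per group will be necessary for the effect size indicated above to lead to a statistically significant result" and then: "A total of 84 patients will therefore need to be enrolled". Allocation is 1:1, and the test is fixed: "A chi-square test will be used for the primary endpoint".

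Section 2.4 lists "the safety and QoL of these patients" among the secondary endpoints and makes all investigators responsible for reporting adverse events.

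**The concern.** Stopping a supplement and leaving a trial are different events, and the article treats them as one. A patient withdrawn before Day 35 has no primary outcome, because there is no other scan. Control patients receive no MI, so this ground for withdrawal can never apply to them. In an open-label trial of patients who already carry KI toxicity, attributing a symptom to MI is a judgement made with the treatment known. Each time the rule operates it therefore removes outcome data from one randomised arm, for a reason connected with treatment.

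The rule also works against the trial's own secondary endpoints, since a patient with an MI side effect leaves before the end-of-MI QoL assessment and further safety follow-up. A later analysis plan cannot recover scans and questionnaires that were never done.

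The sample size, meanwhile, assumes that every enrolled patient is evaluable, although the article itself plans withdrawals on two grounds.

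**Working it through.** **Inputs.** From Section 2.3: response 60% vs 30%, alpha 5% (two-sided taken, since it reproduces the stated number), power 80%, 42 per arm, 1:1, chi-square test. The article gives no withdrawal rate, so 10% is assumed throughout.

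**Step 1: the plan's own figure.** With p̄ = (0.60 + 0.30)/2 = 0.45,

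n = [1.960 × √(2 × 0.45 × 0.55) + 0.842 × √(0.60 × 0.40 + 0.30 × 0.70)]² / 0.30² = 41.97, rounded up to 42.

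The stated 42 per group is reproduced, and 2 × 42 = 84 is exactly the number to be enrolled. Power at 42 vs 42 is Φ[(0.30 − 1.960 × 0.1086)/0.1035] = Φ(0.843) = 80.0%, where 0.1086 and 0.1035 are the standard errors under the null and the alternative. Summing binomial probabilities over all tables that the uncorrected chi-square test rejects gives an exact power of 82.8%.

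**Step 2: power after loss.** A 10% loss leaves 42 × 0.9 = 37.8, taken as 38. Counting lost patients as non-responders keeps 42 per arm but scales the response rate by 0.9 (60% becomes 54%, 30% becomes 27%).

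| Assumed loss | Handling | Comparison | Approximate | Exact |
|---|---|---|---|---|
| None | – | 60% of 42 vs 30% of 42 | 80.0% | 82.8% |
| 10%, both arms | Completers | 60% of 38 vs 30% of 38 | 75.8% | 76.1% |
| 10%, both arms | Non-responders | 54% of 42 vs 27% of 42 | 72.0% | 74.6% |
| 10%, MI arm only | Completers | 60% of 38 vs 30% of 42 | 78.0% | 81.0% |
| 10%, MI arm only | Non-responders | 54% of 42 vs 30% of 42 | 60.9% | 64.4% |

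Small equal losses: 41 vs 41 gives 79.0% approximate and 81.3% exact; 40 vs 40 gives 78.0% and 79.6%.

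**Step 3: bias if withdrawn patients are excluded.** Let d be the share of the MI arm withdrawn and w the response rate those patients would have had. The completer rate exceeds the full-arm rate by (0.60 − d·w)/(1 − d) − 0.60. At d = 10%:
- w = 30%: 0.57/0.90 − 0.60 = +3.3 points
- w = 60%: 0.54/0.90 − 0.60 = 0
- w = 75%: 0.525/0.90 − 0.60 = −1.7 points

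Size and direction both depend on w, on which the article has no information.

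**Step 4: type I error at its worst.** Suppose MI has no effect (30% in both arms), 10% of the MI arm withdraws, and every one of them would have been a non-responder. Completers then show 0.30/0.90 = 33% vs 30%. Exact rejection is 7.2%, against 5.1% at 42 vs 42. Moving to 38 vs 42 with equal rates already gives 5.5%, from the discreteness of the test, so the part due to bias is 5.5% to 7.2%.

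**The case against.** The strongest reply is that the MI ground may never be used. The article reports no known side effects, and its Discussion calls MI almost free of them. With no withdrawals, the rule causes no bias and formula power is 80.0%. This stands, and it makes the problem conditional. It does not remove it: safety remains an endpoint, attribution is unblinded, and KI toxicity can cause losses in both arms without any MI effect.

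Three stronger readings are tempting, and the documents do not support them.

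- A reader might infer that the randomised comparison is already broken. The article does not say that withdrawn patients leave the chi-square analysis. The analysis set and missing-data handling may be in the full protocol or analysis plan, and their absence here is not counted as a fault.
- A reader might infer that MI tolerability is bound to look better than it is. Sections 2.4 and 2.5 require adverse events to be reported with severity, seriousness and causality, so the event that triggers withdrawal is captured. What is lost is what follows it.
- A reader might infer that any withdrawal takes power below 80%. That is true of the normal approximation behind the 42. Exact power starts at 82.8% and is still 81.3% at 41 vs 41 and 81.0% at 38 vs 42.

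**Conclusion.** The concern holds as a conditional risk. Section 2.2 contains a stated rule that, whenever it is triggered before Day 35, loses the primary outcome, end-of-MI QoL and later safety follow-up in the MI arm only. Bias follows only if withdrawals occur, if those patients differ in response, and if they are excluded.

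The enrolment of 84 has no reserve. At an assumed 10% loss, the cost ranges from small (78% approximate, MI-arm loss, completers) to large (61% approximate, MI-arm loss counted as non-response). The large figure depends on how lost patients are handled, and counting one-sided losses as non-response itself weighs against MI. This is why it is better to avoid the loss than to repair it in the analysis.

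**What to change.** In Section 2.2, leave the clinical rule on stopping MI as it is, but separate it from leaving the study. Patients who stop MI stay in follow-up for the Day 30 and Day 35 assessments and for adverse-event reporting, unless they withdraw consent or the scan is clinically precluded. They are analysed in the arm to which they were randomised.

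In Section 2.3, state that 80% power requires 84 evaluable patients. Then give the consequences of an assumed 10% loss:
- **Both arms:** about 76% for completers, or 72% with lost patients counted as non-responders (75% exact).
- **MI arm only:** about 78% for completers (81% exact), or 61% with lost patients counted as non-responders (64% exact).

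Both patterns should appear, because the equal-loss figures alone would be too favourable for a rule that acts in one arm.

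The cost is a less favourable stated power and slightly more follow-up of patients who stop MI. No patients are added and no new procedure is introduced. The change should be made before enrolment, since scans not done cannot be recovered.
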